**5. Safety considerations**

- The participants were informed about the advantages of the study.
- Participants were ensured that there is no risk associated to treatment protocols given in this study
- They were informed that they are free to withdrawal their participation anytime during the study and they will not be penalized if they decided to leave.
- All ethical rules and regulations Ethical Committee of the University were followed while conducting the study while taking care of all rights of participants.
- All the participants were included in the study on the basis of written consent.
- Subjects were kept anonymous throughout the study and their identity will not be revealed in any of the publications.
- All information and collected data remained confidential.

**6. Follow-up**

After first assessment and treatment amputees were ask to continue their exercise plan at home and reassessed after two weeks. During home-based treatments, daily telephonic reminders were given to all of the participants. Research evidence recommends that a treatment protocol of four weeks of mirror therapy may reduce chronic pain. Therefore, therapist collected the data at baseline, and before and after treatment at the end of 2nd and 4th weeks.

**7. Data management and statistical analysis**

Normality of the data was assessed through Shapiro–Wilk test. Multivariate analysis of variance was used to analyse training-induced changes in both groups. Between-group differences were computed with Mann-Whitney U test for VAS (pain) and second domain of SF-36. Independent samples t-test was used for AMP and remaining domains of SF-36. All statistical analyses were done with IBM SPSS 25.0 (*IBM, New York, USA*). Alpha level of significance was set at 0.05.

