**1. Project summary**

The objective of current study is to evaluate the effects of phantom exercises on phantom limb pain, mobility status, and quality of life in lower limb amputees treated with mirror therapy and routine physiotherapy. Twenty-four individuals with lower leg amputation participated in this trial and were randomly assigned to two equal groups. Limb Deficiency and Phantom Limb Questionnaire was used for screening of the participants. Other tools were Visual analogue scale (pain), Amputee mobility predictor (Ambulatory status) and 36-Item Short-Form Health Survey questionnaire (Health-related quality of life). The study was conducted in 12 months and data obtained was analysed through Statistical Package for Social Sciences (SPSS) 25.0 (*IBM, New York, USA*). The intervention lasted for 4 weeks. The control group underwent mirror therapy and conventional physical therapy while the experimental group performed phantom exercises additionally. Data was collected at baseline, after two and four weeks of intervention using. Mean age of the participants in experimental and control groups was 45.3±11.1 years and 40.5±12.5 years respectively. Both groups were comparable at baseline. After intervention, pain was significantly lower in the experimental group (p<0.05). Similarly, the experimental group demonstrated significantly better score in the “bodily pain” domain of SF-36 (p<0.05). Both groups improved in other domains of SF-36 and ambulatory potential with no significantly between-group differences after intervention. It was concluded that addition of phantom exercises resulted in significantly better pain management in lower limb amputees treated with mirror therapy and routine physiotherapy.

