**2. Rationale & background information**

Limb amputation negatively affects psychological, social and physical health of the patients (1). Phantom limb pain (PLP) is a common complaint after lower limb amputation can be defined as discomfort or pain in missing part of the limb. According to the literature, the incidence of PLP ranges from 42.2% to 78.8% of all cases, while the reported prevalence is 45-85% (2). Although PLP subsides with time in most patients irrespective of the cause of amputation, it persists for several years in 5-10% cases (3). PLP is distinguishable from residual limb pain (RLP) since RLP originates from physical impairments such as skin conditions, vascular abnormalities, impaired healing process, neuromas, soft tissue and bone disorders, etc. (4, 5).

One of the foremost causes of PLP is history of chronic pain (e.g., due to diabetes or peripheral vascular disease) in the affected limb before amputation. Other causative factors include seasonal changes, infections, defecation movements, urination, etc. (6). Multiple mechanisms are reported to be involved in PLP, such as spinal, supraspinal and peripheral although there is no consensus on the exact mechanism of PLP (7, 8). It has been suggested that multiple neurological mechanisms are responsible for PLP and RLP (9). PLP may deteriorate several important concepts of health-related quality of life (QOL) such as mood, sleep, independence, emotional health or relationship with family and friends, etc. (10)

One of the methods for subjectively evaluating the limb amputees in detail is limb Deficiency and phantom limb questionnaire (11). Similarly, several strategies and resources are available for evaluating the mental and physical health of amputees during rehabilitation. One of such tools is Amputee Mobility Predictor (AMP) which is an easy and reliable way of assessing ambulatory status of lower limb amputees, with or without the prosthesis. The severity of phantom limb pain can be subjectively assessed with Visual Analogue Scale (12). As for quality of life, one of the more commonly used instrument is 36-Item Short Form Survey (SF-36) which evaluates eight health domains: physical functioning, bodily pain, role limitations due to physical health problems, role limitations due to personal or emotional problems, emotional well-being, social functioning, energy/fatigue, and general health perceptions (13).

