**4. Methodology**

*4.1 Patient information*: The mean (standard deviation) age of patients in the experimental and control group was 45.3(11.1) years and 40.5(12.5) years correspondingly. Vast majority of the patients underwent amputation within 2 years prior to this trial (experimental group =10; control group = 11). The number of male patients in experimental and control group was 8 and 9 respectively. Most patients reported right-handedness except for 1 patient in each group. The patients were recruited via non-probability convenience sampling. Thirty lower limb amputees were screened for eligibility through Limb Deficiency and Phantom Limb Questionnaire among other criteria.

*4.2 Eligibility Criteria:*

*4.2.a Inclusion Criteria:*

- Ages Eligible for Study: 18 Years to 50 Years (Adult)
- Accepts Healthy Volunteers: No
- Unilateral lower limb amputation
- Phantom limb pain score (40-100 on VAS)
- Either gender
- Stable prosthetic situation (i.e., satisfaction with the fitting of the prosthesis) or being a non-user.

*4.2.b Exclusion Criteria:*

- Amputees with psychological/neurological impairments.
- Amputees having neuropathic pain other than phantom limb pain.
- Patients having visual-spatial impairments.
- Taking pain relief medications will also be excluded.
- Patients having residual limb pain.
- Inability to give informed consent.
- Carcinoma
- Infectious stump
- Severe hearing loss
- Any condition that restricts the movement of opposite limb, pain or limited range of motion in the intact limb
- Infectious and systematic diseases

*4.3 Sample size:* Sample size is 6 in each group calculated by openEpi (24). We included 12 patients in each group.

*4.4 Setting:* Pakistan Society for the Rehabilitation of the Disabled (PSRD) and Hope foundation for rehabilitation sciences, Lahore, Pakistan.

*4.5 Rehabilitation protocols*: Both study groups received mirror therapy (15 minutes) and routine physical therapy (20 minutes) while the experimental group was given Phantom Motor Execution (PME), also known as phantom exercises, additionally (15 minutes).

*4.5.a Phantom Motor Execution:* Phantom exercises included imagining movement of the phantom limb and attempting to execute these movements. The patients were asked:

1. About position at which they were feeling their phantom limb.
2. To place their intact limb at same position as they felt their phantom limb.
3. To move their both limbs in opposite direction.

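### Change over time within the arms is labelled training-induced, but without an untreated arm it cannot be attributed to training; effect claims should rest on the randomised contrast

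*Combined protocol and SAP*

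**What the plan says.** Sections 4.10 and 7 carry the same text. After a Shapiro-Wilk check, "Multivariate analysis of variance was used to analyse training-induced changes in both groups". The next sentences deal with the comparison of the arms: "Between-group differences were computed with Mann-Whitney U test for VAS (pain) and second domain of SF-36", with independent-samples t-tests for AMP and the other SF-36 domains. Neither section names the factors, dependent variables or visits of the MANOVA.

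Four other statements bear on how change over time can be read:

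- Section 4.2.a sets a threshold on a primary outcome as an entry condition: "Phantom limb pain score (40-100 on VAS".
- Section 2 says of the natural course: "Although PLP subsides with time in most patients irrespective of the cause of amputation, it persists for several years in 5-10% cases".
- Section 4.1 reports: "Vast majority of the patients underwent amputation within 2 years prior to this trial (experimental group =10; control group = 11". That is 10 + 11 = 21 of 24 participants.
- Section 4.5 says: "Both study groups received mirror therapy (15 minutes) and routine physical therapy (20 minutes". Phantom exercises were added in one arm only, so no arm was untreated.

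The project summary (section 1) reports: "Both groups improved in other domains of SF-36 and ambulatory potential with no significantly between-group differences after intervention".

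**The concern.** The label assigns a cause that the design cannot identify. Change from baseline in a treated arm is the sum of any treatment effect, the natural course of phantom pain and the effect of repeated testing. For VAS, regression to the mean is added because patients had to score at least 40 to enter. No section says how these are to be separated.

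What is at stake is mainly the outcomes on which the arms did not differ. For the SF-36 domains other than bodily pain, and for AMP, the summary reports improvement in both groups and no significant difference between them. On those outcomes within-arm change would be the only support for a benefit of either programme, and it cannot carry that claim.

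**Working it through.** The plan gives no figure to reproduce on this point: it states no VAS mean, SD or retest correlation for the source population and no rate of spontaneous decline. All of these are assumptions below.

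**1. Reading of the MANOVA sentence.** It is assigned to changes in both groups, and the between-group differences then get their own named tests for VAS, AMP and every SF-36 domain. If the MANOVA were the randomised comparison, the later tests would duplicate it. Change over time within the arms is therefore the natural reading, though still an inference.

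**2. Regression to the mean on VAS.** For a normal source population selected at 40 or more, with no treatment effect and no natural decline:

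expected fall = (1 − r) × SD × λ, where λ = φ(a) / (1 − Φ(a)) and a = (40 − mean) / SD.

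- Mean 50, SD 20: a = −0.5, λ = 0.3521 / 0.6915 = 0.509.
  - r = 0.7: 0.3 × 20 × 0.509 = 3.1 mm
  - r = 0.5: 0.5 × 20 × 0.509 = 5.1 mm
- Mean 45, SD 25: a = −0.2, λ = 0.3910 / 0.5793 = 0.675.
  - r = 0.7: 0.3 × 25 × 0.675 = 5.1 mm
  - r = 0.5: 0.5 × 25 × 0.675 = 8.4 mm

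**3. Wider inputs.** With source mean 40-60 mm, SD 15-25 mm, r 0.5-0.9 and the upper limit of 100 also applied, the expected fall runs from 0.3 mm (mean 60, SD 15, r 0.9) to 9.6 mm (mean 40, SD 25, r 0.5).

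**4. Effect on significance tests.** Simulation of 20,000 trials per setting, 12 per arm, no treatment effect. A paired t-test at two-sided 0.05 stands in for the unspecified MANOVA, so the nominal rate for a significant fall is 2.5%.

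| Setting | Significant fall in a given arm | In both arms | Over all 24 |
|---|---|---|---|
| Selection only, range over step 3 inputs | 3% to 28% | 0.1% to 8% | 4% to 53% |
| Mean 50, SD 20, r 0.7, plus 5 mm spontaneous fall | 39% | 15% | 71% |
| Same, plus 10 mm spontaneous fall | 79% | 62% | 98% |

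The between-arm comparison at follow-up was significant in 4.7% to 5.4% of simulated trials by t-test. A spot check by Mann-Whitney (mean 50, SD 20, selection only) gave 4.1% to 4.5%. Selection and spontaneous decline act alike on both randomised arms and leave that test at its nominal level.

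**5. Which outcomes the figures cover.** Steps 2 to 4 apply to VAS. SF-36 and AMP had no entry threshold, so regression to the mean reaches them only indirectly; natural recovery and repeated testing are the likelier alternatives there. The documents allow no figure for either.

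**The case against.** The strongest reply is that nothing important depends on this sentence. The plan names a between-group test for every outcome, the pain conclusion in section 1 rests on the difference between the arms, and the statement that both groups improved is descriptive and sits beside the report of no group difference. Section 2 gives no rate of decline, and a time since amputation of under two years does not establish a material fall over four weeks. The millimetre figures rest on assumed inputs and concern VAS, not the outcomes in the both-groups sentence.

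Most of this stands. It limits the point to how the change analysis is labelled and interpreted. It does not rescue the label, because the causal wording is in the analysis sections themselves and the design offers no comparator to support it.

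A reader might also draw stronger conclusions that the documents do not support:

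- *That the pain result is biased.* It is a randomised contrast, and these influences are expected equally in both arms.
- *That the MANOVA could not be computed with 12 per arm because it had too many variables.* The documents do not say that all outcomes and visits were entered jointly. One analysis per outcome with two change variables leaves 12 − 2 = 10 denominator degrees of freedom within an arm.
- *That the week-2 and week-4 data were withheld from the between-group comparison.* No section says which visits those tests use.

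A last objection concerns the remedy. A mixed model also assumes normal residuals, whereas the plan's use of Mann-Whitney suggests non-normal VAS and second-domain scores. That is fair, and the fix has to provide for it.

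**Conclusion.** The concern holds as a point about attribution. Change within the arms cannot be called training-induced, and improvement of both groups in SF-36 domains and AMP is not evidence that either programme worked. For VAS, the part due to the entry rule alone is about 3-8 mm if the source mean is 45-50 mm, the SD 20-25 mm and the retest correlation 0.5-0.7. It can be as small as 0.3 mm if the source mean is well above 40 and the correlation high. Any natural decline adds to it by an unknown amount. For SF-36 and AMP the conclusion is qualitative.

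It rests on reading the MANOVA as a change-over-time analysis. If a group-by-time term was meant, that would be a between-arm test and the attribution problem would not apply to it, but the sentence would still have to say so. The reported between-group pain result is unaffected.

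**What to change.** In sections 4.10 and 7, replace the MANOVA sentence with one repeated-measures model per outcome on the week-2 and week-4 values, with terms for baseline value, group, visit and group-by-visit and with small-sample degrees of freedom. Report the group difference at week 4 as the effect. Keep the Mann-Whitney test as a sensitivity analysis for VAS and the second SF-36 domain. Section 6 mentions readings before and after treatment at the end of weeks 2 and 4, so state which reading is the visit value.

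Present within-arm means and SDs as changes from baseline, without p-values. In section 1, do not present improvement of both groups as a treatment effect.

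No new data are needed. The cost is rewording, a re-run on the existing data and the loss of within-arm significance statements.

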4. To return back to their starting position. (24)

The movements included ankle inversion/eversion, flexion/extension, adduction with flexion of toes as clenching, abduction with extension of toes as unclenching. After patient feel relaxation, movements as knee flexion/ extension or hip flexion/ extension were repeated, until the PLP disappeared. (19) Phantom exercises were repeated until the PLP subsided completely with a maximum of 15 repetitions in one session.

*4.5.b Mirror therapy*: A standing flat mirror was used to perform 15 minutes of mirror therapy under physiotherapist’s supervision every day for 4 weeks. Sources of external stimulations (noise, television) were minimized, all accessories on the sound limb were removed, and patient’s comfort was ensured before the start of each session. Goals and benefits of mirror therapy were explained to the patients who were encouraged to ask questions. Pain level was measured on VAS prior to each session and rules of mirror therapy were instructed.

*4.5.c Routine physiotherapy*: The regimen comprised stretching of the tight musculature, static and dynamic muscle strengthening. Participants were also advised to keep a log of nature, frequency and duration of their physical activities. (20)

*4.6 Primary Outcome Measures:*

*4.6.a Visual analogue scale (VAS)* [ Time Frame: 4 weeks]

changes from the baseline, the visual analogue scale The VAS evaluates pain subjectively. It consists of a 100-mm line, with two endpoints representing "no pain" to "worst pain imaginable from left to right." Patients are instructed to mark on the line according to the level of pain and the same is measured

*4.6.b Amputee Mobility predictor* [ Time Frame: 4 weeks]

changes from the baseline, Amputee mobility predictor (AMP) is an amputee-specific tool for predicting ambulatory potential. This clinical test evaluates the predicted mobility of amputee with and without a prosthesis The AMP is a clinical test consisting of 20 tasks that are given a score of 0, 1, or 2 based on the amputee's performance. There is an item 21 where a score is given ranging from 0 to 5.

*4.6.c Limb Deficiency and Phantom Limb Questionnaire* [ Time Frame: day 1]

Patients will be evaluated using "Limb Deficiency and Phantom Limb Questionnaire (Questionnaire 2008, Version 2)" in order to assess their eligibility for including in this study.

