This questionnaire does not have any scoring, it only concludes the questions on Yes/No basis for presence or absence of phantom limb pain.

*4.7 Secondary Outcome Measures:*

*4.7.a Short form 36 (SF-36)* [ Time Frame: 4 weeks]

changes from the baseline, the 36-Item Short-Form Health Survey questionnaire (SF-36) is a very popular instrument for evaluating Health-Related Quality of life (HRQOL). It is a widely used valid and reliable tool for measuring the (HRQOL) and it can be employed in both the healthy and diseased population such as amputees for assessing the outcome of health care services and the effect of medical intervention.

The SF-36 measures eight scales: physical functioning (PF), role physical (RP), bodily pain (BP), general health (GH), vitality (VT), social functioning (SF), role emotional (RE), and mental health (MH). Component analyses showed that there are two distinct concepts measured by the SF-36: a physical dimension, represented by the Physical Component Summary (PCS), and a mental dimension, represented by the Mental Component Summary (MCS).

*4.8 Equipment:*

Therapy mirror: A standing mirror (130 cm × 46 cm) with wooden frame and base (62 cm × 65 cm)

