*4.9 Data collection*: Data was collected at baseline and at 2-week intervals until the conclusion of 4-week interventions. Visual Analogue Scale was used to quantify the intensity of pain before, during, and after the interventions. The ambulatory potential of the patients was assessed with the Amputee Mobility Predictor which consists of 21 different tasks with a maximum overall score of 39 signifying best ambulatory potential. High inter- and intra-rater reliability has been reported for AMP in the literature. Quality of life was evaluated through 36-Item Short Form Survey (SF-36) which addresses eight health domains: physical functioning, bodily pain, role limitations due to physical health problems, role limitations due to personal or emotional problems, emotional well-being, social functioning, energy/fatigue, and general health perceptions. 24 patients were randomly allocated into two groups; Interventional group and control groups. To ensure that the patients knew the differences between residual limb, phantom limb, and between phantom limb pains and postoperative wound pains rather than a questionnaire, a proper interview was conducted. Demographics and detail information about their amputation was collected using Limb Deficiency and phantom Limb Questionnaire. After which participants were guided about their treatment plan and therapist demonstrated all relevant exercises. A specially designed Boucher having illustrations and detailed information about mirror therapy and phantom exercises was also provided to all participants. For the convivence of responders in both groups all the instruction given verbally or written in brochure was in native language Urdu. All assessments were performed by the same physical therapist (AZ) at all stages of data collection for all patients.

*4.10 Data analysis*: Normality of the data was assessed through Shapiro–Wilk test. Multivariate analysis of variance was used to analyse training-induced changes in both groups. Between-group differences were computed with Mann-Whitney U test for VAS (pain) and second domain of SF-36. Independent samples t-test was used for AMP and remaining domains of SF-36. All statistical analyses were done with IBM SPSS 25.0 (*IBM, New York, USA*). Alpha level of significance was set at 0.05.

*4.11 Consort diagram:*

[figure not shown]

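### The between-group tests name no baseline covariate, do not say whether final or change scores are tested, and leave the test behind SF-36 bodily pain unfixed

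*Combined protocol and SAP*

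**What the plan says.** Sections 4.10 and 7 carry the same analysis text. VAS and one SF-36 domain are covered by "Between-group differences were computed with Mann-Whitney U test for VAS (pain) and second domain of SF-36", everything else by "Independent samples t-test was used for AMP and remaining domains of SF-36". A multivariate model is also named: "Multivariate analysis of variance was used to analyse training-induced changes in both groups". It has no stated covariate, no group-by-time term and no stated role in the comparison of groups. The significance level is given ("Alpha level of significance was set at 0.05"), but not whether tests are two-sided.

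Sections 4.9 and 6 record measurements at baseline, week 2 and week 4. Section 4.6.a introduces the pain outcome as "changes from the baseline, the visual analogue scale", and AMP (4.6.b) and SF-36 (4.7.a) are introduced in the same way.

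The SF-36 domains are listed in two orders. Section 4.7.a has "physical functioning (PF), role physical (RP), bodily pain (BP), general health (GH", which puts role physical second. Section 4.9 "addresses eight health domains: physical functioning, bodily pain, role limitations due to physical health problems", which puts bodily pain second, and section 2 uses that same order. Section 1 reports a between-group difference in VAS pain and in SF-36 bodily pain, and none in the other SF-36 domains.

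**The concern.** There are two gaps.

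First, the quantity being compared is open. A final-score test, a change-score test and a baseline-adjusted test can give different estimates and p-values from the same 24 patients, and the plan does not say which of the first two was run. Neither uses the baseline value as a covariate. In arms of 12, chance differences at baseline are sizeable. A final-score comparison carries part of them forward, and a change score over-corrects when the correlation is below 1. No effect estimate with a confidence interval is planned.

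Second, a domain is identified only by its position in a list, and the lists disagree. On one order bodily pain was tested by Mann-Whitney, on the other by a t-test. It is the only SF-36 domain for which a difference is claimed, so the reader needs to know which.

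**Working it through.** **The plan's own figure.** Section 4.3 says "Sample size is 6 in each group calculated by openEpi (24", and 12 per group were included. No effect size, SD or power is given, so the 6 cannot be reproduced. Worked backwards with an assumed 80% power and two-sided 0.05, it implies a standardised difference of (1.960 + 0.842) × sqrt(2/6) = 1.62. For 12 per arm the same formula gives 2.802 × sqrt(2/12) = 1.14. An assumed effect of 1.2 SD is therefore close to what 12 per arm can detect.

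**Chance baseline imbalance.** One standard error of the difference in baseline means is sqrt(2/12) = 0.41 SD. With equal variances and correlation r, a final-score comparison carries r times the imbalance and a change-score comparison carries (r − 1) times it. At r = 0.5 these are +0.20 SD and −0.20 SD.

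**Power at 12 per arm.** Inputs: n = 12 (section 4.3) and alpha 0.05 (section 7). Assumed: two-sided testing, normal data, an effect of 1.2 SD, and r, which is not in the documents. The variance of the estimated difference is (2/12) × f, where:

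- final-score t-test: f = 1, 22 df
- change-score t-test: f = 2(1 − r), 22 df
- ANCOVA: f = (1 − r²) × 21/20, 21 df; the 21/20 is the price of estimating the slope

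At r = 0.5 the ANCOVA factor is 0.75 × 1.05 = 0.7875. That is a 21% lower variance, equivalent to 1/0.7875 = 1.27 times the patients. The noncentrality is 1.2 / sqrt(0.1667 × 0.7875) = 3.31, against 1.2 / 0.408 = 2.94 for the final-score t-test.

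Power in per cent (t-tests and ANCOVA from the noncentral t; Mann-Whitney from 40,000 simulated trials per row):

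| r | t, final | Mann-Whitney, final | t, change | Mann-Whitney, change | ANCOVA |
|---|---|---|---|---|---|
| 0 | 80.2 | 76.6 | 51.1 | 47.0 | 78.1 |
| 0.3 | 80.2 | 76.6 | 66.1 | 62.1 | 81.8 |
| 0.5 | 80.2 | 76.4 | 80.2 | 76.8 | 88.4 |
| 0.7 | 80.2 | 76.3 | 95.2 | 93.6 | 96.9 |

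Simulated ANCOVA power agreed (88.7% at r = 0.5), and its type I error was 4.8 to 5.1%.

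**Where the gain stops.** On variance alone, ANCOVA beats the final-score t-test when (1 − r²) × 21/20 < 1, that is r > sqrt(1/21) = 0.22. The lost degree of freedom moves this to about 0.23. Below that the loss is small, 2.1 points at r = 0 in the table.

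**Skewed data** (shapes assumed, 1.2 SD effect). With a moderately skewed gamma distribution (shape 4) and r = 0.5, Mann-Whitney reached 81% on final scores and 79% on change, and ANCOVA 89%. At r = 0 Mann-Whitney was slightly ahead, 82% against 80%. With a heavily skewed lognormal follow-up (log-SD 0.9), Mann-Whitney on final scores reached about 96% at every r tried. ANCOVA reached 83% (r = 0), 88% (r = 0.5) and 90% (r = 0.7), so there the order reverses.

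**The SF-36 label.** Section 2: bodily pain second. Section 4.7.a: role physical second, bodily pain third. Section 4.9: bodily pain second. Two of the three lists make bodily pain the Mann-Whitney domain; the third gives it a t-test. In simulated normal samples of 12 per arm with effects of 0.6 to 1.2 SD, the two tests disagreed on significance in 6.2 to 7.8% of samples.

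**The case against.** The strongest reply is that baseline may already be in the analysis. The outcomes are defined as changes, so the tests may have been run on change scores. In that case a baseline difference does not simply pass into the result, and at r = 0.7 the gap to ANCOVA is only about 2 to 3 points. This stands. A reader might infer that baseline was ignored; the documents do not show that. They show no covariate and an unstated score.

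Unadjusted tests after randomisation also keep their type I error, so this is a question of precision and clarity. A reader might infer that the reported pain result is invalid, and nothing here supports that.

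Section 1 says the groups were comparable at baseline. If that rests on a significance test, it gives limited comfort: a difference would have to exceed about 2.07 × 0.41 = 0.85 SD to reach p < 0.05.

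The power gain depends on r. The VAS entry range of 40 to 100 (section 4.2.a) could lower it, and outcomes assigned Mann-Whitney may well be skewed. Both points stand and limit the claim.

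A reader might also infer that a Shapiro-Wilk result decided each test. The plan says only that normality was assessed; no rule links it to the choice.

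Finally, the domain list in 4.9 comes directly before 4.10 and agrees with section 2, so bodily pain is the likelier meaning. That makes the ambiguity small, but it does not remove it.

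**Conclusion.** The point holds in a limited form. Two parts rest on the text alone: the between-group tests name no baseline covariate and do not state score or visit, and the SF-36 domain given Mann-Whitney cannot be identified with certainty.

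The gain from ANCOVA is conditional. With normal data, a 1.2 SD effect and r = 0.5, it is about 8 points of power over the t-test and 12 over Mann-Whitney. Over the final-score t-test there is little or no gain below r of about 0.23. Over Mann-Whitney on final scores there can be a loss if the data are heavily skewed. The claim that ANCOVA is always more powerful is therefore not supported. ANCOVA alone would not settle the role of the multivariate model, the use of week 2, or multiplicity across VAS, AMP and eight SF-36 scales.

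**What to change.** 1. In 4.10 and 7, replace the positional reference with the name of the SF-36 domain actually tested by Mann-Whitney, and put the lists in 2, 4.7.a and 4.9 in one order. State whether final or change scores were tested and at which visit. Section 6 records data before and after treatment at weeks 2 and 4, so say which reading was used.
2. Add a baseline-adjusted re-analysis: ANCOVA of week-4 VAS, AMP and each SF-36 scale, with group and the same measure at baseline in the model. Report the adjusted difference with its 95% CI, and a p-value from permuting group labels because VAS may be skewed. The power of the permutation version was not computed here.
3. Label this plainly as a re-analysis added after results were known, since section 1 already reports them. It should not replace the description of what was done.
4. Keep the reported Mann-Whitney and t-test results beside it.

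The cost is a few sentences, one degree of freedom per model, and a re-run on data already held.
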